#### Secondary Outcomes

The secondary outcomes are well-being (Clinical Outcomes in Routine Evaluation 10 [CORE-10]) [44] and 4 psychological flexibility process variables, namely committed action (the Valuing Questionnaire’s Progress scale comprised of items 3, 4, 5, 7, and 9) [45], mindfulness (Southampton Mindfulness Questionnaire) [46], cognitive defusion (Cognitive Fusion Questionnaire) [47], and experiential avoidance (Brief Experiential Avoidance Questionnaire) [48].

#### Other Clinical Outcomes

A facilitator will rate illness severity at enrollment and before the start of the group using the “Clinical Global Impression–Severity” scale and will rate illness improvement at the end of the group and at the booster session using the “Clinical Global Impression–Improvement” scale [49,50].

#### Consumer and Facilitator Feedback

Permission will be sought from participants to use their responses to routine qualitative feedback questions for evaluation purposes. These questions ask about their hopes and expectations for the group (at T0), helpful and unhelpful aspects of the group (at T2 and T3), requests for remaining sessions (at T2), and reflection on any perceived changes attributed to the group (at T3 and T4). The method of collecting these routine feedback responses is dependent on the site. The baseline feedback questions (at T0) are typically asked and recorded by a facilitator during the “Information and Engagement” session; the feedback questions at other time points are typically written responses by participants. Qualitative data about the group will be sought from facilitators who consent to participate in a semistructured interview after completing a group. The qualitative interview will assess the feasibility of the group, its evaluation in routine practice, and perceptions of the group program’s effectiveness.

In addition, during the initial consent process, participants will be asked for written consent to contact them in the future to invite them to participate in a follow-up study involving a qualitative interview exploring their experience of participating in the group.

### Statistical Methods and Sample Size

We intend to use an intention-to-treat sample to test a univariate latent growth curve model of the primary outcome from before the start of the waitlist period to the start of the group to the booster session in order to compare the trajectory over the waitlist period to the trajectory over the active treatment period. We selected this method of analysis to strengthen our estimations of associations due to the limitations of the nonrandomized study design chosen as the most realistic option for an evaluation of a program already in routine practice [51]. A minimum sample size of 90 is required to conduct the proposed growth curve structural equation model (5 observed variables and 2 latent variables) with an anticipated medium effect size (0.3), α set at .05, and power (1–β) at .80. Univariate latent growth curve models for each of the 5 secondary outcomes will also be tested. If there are sufficient data, we will test whether the trajectory of the 4 psychological flexibility process variables from the start of the group to the midpoint session (T1 to T2) is significantly associated with the trajectory of personal recovery (T2 to T4) using multivariate growth models. We do not predict a priori any differences associated with the study site. We intend to calculate the ICC after the data are collected to determine the relatedness of the data collected at different study sites.

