### Objectives

The primary aim is to evaluate the effectiveness of the Recovery ACT group program on personal recovery for adults living with a psychotic disorder in routine clinical practice across public mental health organizations in Australia using a single-group, waitlist control design. A secondary aim is to evaluate the effect of the Recovery ACT group program on well-being and psychological flexibility processes (experiential avoidance, cognitive defusion, engagement in valued actions, and mindfulness). The research questions are as follows: (1) What are the clinical benefits and risks of the Recovery ACT group program for adults diagnosed with psychotic disorders as conducted in routine practice in Australia? (2) Are there changes in psychological flexibility processes due to participation in the Recovery ACT group program? (3) Are changes in psychological flexibility processes associated with changes in personal recovery and well-being?

The primary and secondary hypotheses are that the longitudinal trajectory of personal recovery and the secondary outcomes will not significantly change over the waitlist period, then will improve from the start to the end of the group program, and then improve at a less rapid rate from the end of the group to the booster session. A further hypothesis is that changes in psychological flexibility processes during the first half of the group program will be associated with changes in personal recovery and well-being in the second half of the group program.

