### Study Design

This trial is a multiagency, prospective, longitudinal, nonrandomized, waitlist control, single-group study among Australian adults diagnosed with a psychotic disorder who participate in a routine Recovery ACT group program. The design includes 4 assessment time points: the start of the waitlist period (approximately 4-6 weeks before the start of the group program), the start of the group program (0 weeks), the end of the group program (about 6 weeks after the start of the group program), and the booster session (about 10 weeks after the start of the group program). Some participants may complete outcome measures at the midpoint session (T2, which is 3 weeks after the start of the group program) if the study site is resourced to collect data at an additional time point. Quantitative data from facilitators about participants’ clinical severity and clinical improvement will be collected before, during, and after the group program, as well as relevant demographic and clinical information collected at baseline from participants’ electronic medical records. At either the end of session 7 or the booster session, participants will be asked to provide written consent for study personnel to contact them for a follow-up study. Facilitators will be invited to complete a semistructured interview with senior investigators after each group program to gather qualitative data about the feasibility of the group program in routine practice and to assist in the interpretation of the quantitative measures completed by participants. The protocol development addressed the SPIRIT (Standard Protocol Items: Recommendations for Interventional Trials; Multimedia Appendix 1) guidelines [36] and intends to adhere to the CONSORT (Consolidated Standards of Reporting Trials; Figure 1) criteria [37]. We retrospectively registered the trial with the Australian New Zealand Clinical Trials Registry; Table 1 lists the trial registration data set.

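### The 90-participant, 80% power figure is stated for a two-latent-variable growth model and an undefined effect of 0.3, so 80% power for the primary waitlist-versus-group comparison is not shown

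*Protocol article*

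**What the plan says.** Under Statistical Methods and Sample Size, the protocol article plans a univariate latent growth curve model of the QPR to "compare the trajectory over the waitlist period to the trajectory over the active treatment period". Randomization and Blinding repeats that comparison, with each participant as their own control. Objectives gives the expected shape: no material change while waiting, improvement across the group program, and "then improve at a less rapid rate from the end of the group to the booster session".

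The sample size sentence in the same statistical section reads: "A minimum sample size of 90 is required to conduct the proposed growth curve structural equation model (5 observed variables and 2 latent variables". Its other inputs are a medium effect of 0.3, alpha .05 and power .80. It does not name the two latent variables, say whether loadings are fixed or free, or say what parameter 0.3 measures.

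Study Design states "The design includes 4 assessment time points" (T0, T1, T3 and T4). The midpoint, T2, is collected only where a site has the resources. Participants and Study Setting gives a target of 160 and expected retention of 60%.

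**The concern.** In a univariate growth model, two latent variables ordinarily mean an intercept and one slope. With linear loadings, that single slope runs through the waitlist, group and post-group periods alike. It offers nothing with which to test whether change during the program exceeds change during the wait, and it cannot bend to follow the hypothesised three phases. Separate waitlist and group slopes need at least one more growth factor. The count of five observed variables also includes an occasion that the design does not require.

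Two misreadings are at stake. A null result could be taken as coming from a trial with 80% power for its main question. And if a single-slope model were fitted, steady natural improvement would appear as a significant slope with no program effect at all, which is what the waitlist period is there to guard against.

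**Working it through.** **Inputs from the protocol article.** N = 90, effect 0.3, alpha .05 (two-sided assumed), power .80; 160 recruited at 60% retention; T1 to T3 = 6 weeks, T4 at about week 10, wait of 4 to 6 weeks; QPR test-retest ICC 0.74.

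**Assumptions.** Equal correlation r between all occasions, with the ICC of 0.74 used as r; outcome SD of 1; complete data; 5-week wait as the central case.

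**1. Reproducing 90.** The article names no formula. Two routes reach it.

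- Closed-form lower bound for detecting a correlation of r = 0.3 between two latent variables: A = 1 − r² = 0.91; B = r·asin(r/2) = 0.0452; C = r·asin(r) = 0.0914; D = A/√(3 − A) = 0.6295; H = (0.3/2.8016)² = 0.01147; q = A(π/6 − B + D) + H = 1.0196. Then n = [q + √(q² + 4AH(π/6 + √A + 2B − C − 2D))]/(2H) = (1.0196 + 1.0241)/0.02293 = 89.1, so 90.
- Paired t-test with standardised effect 0.3 (noncentral t): power 0.799 at 89 and 0.804 at 90, so 90.

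A Fisher z test of a correlation of 0.3 gives 85, which does not match. The arithmetic behind 90 is therefore sound, but the number does not identify the quantity powered.

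**2. Power for the primary contrast, if 0.3 is in outcome SDs.** For a wait of w weeks, the slope difference per person is (Y3 − Y1)/6 − (Y1 − Y0)/w. The coefficients sum to zero, so under equal correlation

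Var = (1 − r)·[1/36 + (1/6 + 1/w)² + 1/w²].

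With r = 0.74 and w = 5: 0.26 × (0.0278 + 0.1344 + 0.0400) = 0.0526.

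- SE over 6 weeks at n = 90: 6 × √(0.0526/90) = 0.145 SD.
- Power for 0.3 SD: Φ(0.3/0.145 − 1.96) = 54%.
- Difference detectable with 80% power: 2.80 × 0.145 = 0.41 SD.
- At the expected 160 × 0.60 = 96: SE = 0.145 × √(90/96) = 0.140, power about 57%, detectable difference 0.39 SD.

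Varying both assumptions, n = 90:

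| r | Wait | SE (SD) | Power for 0.3 SD | Detectable at 80% |
|---|---|---|---|---|
| 0.60 | 4 weeks | 0.206 | 31% | 0.58 SD |
| 0.74 | 4 weeks | 0.166 | 44% | 0.46 SD |
| 0.74 | 5 weeks | 0.145 | 54% | 0.41 SD |
| 0.74 | 6 weeks | 0.132 | 63% | 0.37 SD |
| 0.85 | 6 weeks | 0.100 | 85% | 0.28 SD |

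**3. Power if 0.3 is already standardised on the contrast.** The per-person SD of the 6-week contrast is 6 × √0.0526 = 1.376 outcome SDs. An effect of 0.3 in those units is 0.3 × 1.376 = 0.41 outcome SDs, and 90 participants do give 80% power for it. The two readings of 0.3 thus correspond to 0.30 and 0.41 QPR SDs.

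**4. What one linear slope would test.** Take a steady drift of 0.2 SD per 6 weeks with no program effect, at weeks −5, 0, 6 and 10. The mean time is 2.75 and the sum of squared deviations is 130.75. The slope is 0.2/6 = 0.0333 per week; its SE is √(0.26/(130.75 × 90)) = 0.0047; z = 7.1.

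**The case against.** The strongest reply is that the article never says single slope. A two-factor model can have an intercept and one shape factor with freed loadings. On four occasions its two factor means and two free loadings can follow any set of four means, including flat, rising, then rising more slowly, and the periods can be compared through the loadings. This stands: a reader might infer that no two-factor model can test the primary comparison, and that is too strong. Such a model does force individual change in each period to be proportional, and nothing in the text indicates it was intended. The z of about 7 applies only if the loadings are linear.

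Second, a reader might infer that the stated 80% is definitely not the power of the primary test. The document does not support that either. With 0.3 undefined, it could be the standardised contrast, and then 90 is right. What remains is that 80% is not shown.

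Third, the 54% rests on assumptions the article does not make, and the joint range of 31% to 85% crosses 80%. That is fair, and it is why the range must accompany the figure.

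Fourth, T2 is a declared occasion and growth models can use measurements available for only some participants. That is also true; the weakness is only that the sample size basis counts it as one of five without qualification.

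Finally, factor naming and covariance structure may sit in a fuller document. But the article itself states the model's dimensions, effect, alpha, power and N, and read in the ordinary way these do not fit its stated comparison.

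**Conclusion.** The concern holds in this form: the stated sample size basis does not establish 80% power for the waitlist-versus-group comparison. The model it describes has no parameter for that comparison on its usual reading, and its effect size is attached to nothing. The size of the gap depends on what 0.3 means: none if it is the standardised contrast, and about 54% power instead of 80% if it is 0.3 outcome SDs, given r = 0.74, a 5-week wait, equal correlations and complete data.

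It would be tempting to conclude that the trial is too small, since the two-latent-variable bound gives 119 with three latent variables and 137 with four, against 96 expected. Those figures should not be used as required sample sizes. They power correlations between latent variables rather than a slope difference, and nothing in the article says that this bound was used.

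**What to change.** Before any analysis, in Statistical Methods and Sample Size:

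- Replace the count of five observed and two latent variables with a piecewise growth model on T0, T1, T3 and T4, using T2 where available. Give it separate mean slopes for the waitlist, group and post-group periods, and a covariance structure that four occasions can support (for example a random intercept or an unstructured covariance, not three random slopes).
- Name the group slope minus the waitlist slope as the primary, powered contrast.
- Say what 0.3 means on that contrast and in which units. Then restate the power or the detectable difference at the expected 90 to 96 participants, with the assumed correlation and wait.

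The cost is wording and one recalculation. The Results section reports that no analysis has been done, so the change can still be made without knowledge of the outcome. No extra recruitment is needed. The drawback is that the stated power will probably look less favourable.

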#### Primary Outcome

The primary outcome is personal recovery, as measured by the 15-item version of the Questionnaire about the Process of Recovery (QPR) [40,41]. The 15-item QPR has good internal consistency (QPR total α=.89), fair to good test-retest reliability (QPR total intracluster correlation coefficient [ICC]=0.74), moderate sensitivity to change, and adequate convergent validity [42]. The QPR is a measure that assesses the 5 core processes of personal recovery that comprise the “Connectedness; Hope and optimism about the future; Identity; Meaning in life; and Empowerment” (CHIME) framework [43], which is currently the strongest conceptualization of personal recovery in serious mental illness. The Recovery ACT group program seeks to support change in these dimensions for participants.

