#### Randomization and Blinding

This study is a nonrandomized (unblinded) trial that uses a single group, waitlist control, and a quasiexperimental design. All participants serve as their own control. The data for all participants on change in outcomes over the waitlist period (no active intervention) will be used to compare with the data on change in outcomes during the active intervention. The planned statistical methods will strengthen our conclusions. The risk of researcher bias is lessened by the self-report format of the primary and secondary outcomes and the opportunity for participants to submit questionnaires in a sealed envelope.

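### The 80% power at 90 participants is not tied to the primary comparison of waitlist and treatment trajectories; if 0.3 means one standardised change, power for that comparison is about 25% to 37%

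*Protocol article*

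**What the plan says.** Statistical Methods and Sample Size gives the purpose of the latent growth curve model: "in order to compare the trajectory over the waitlist period to the trajectory over the active treatment period". Randomization and Blinding repeats it: each participant is their own control, and change over the waitlist "will be used to compare with the data on change in outcomes during the active intervention".

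The only power statement is in Statistical Methods and Sample Size: "A minimum sample size of 90 is required to conduct the proposed growth curve structural equation model". The model behind that number has five measured and two latent variables, the significance level is 5% and the target power is 80%. The effect enters as a single value, described as medium and equal to 0.3. The statement gives no scale for the 0.3, no parameter it refers to, no sidedness and no correlation between visits.

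Study Design puts the waitlist assessment about 4 to 6 weeks before the group, the end of the group at about 6 weeks and the booster at about 10 weeks. Primary Outcome describes the 15-item QPR as having "fair to good test-retest reliability", with an ICC of 0.74. That is the only correlation-type figure for the outcome.

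**The concern.** A power figure should belong to the comparison that the trial is built to make. Here that is waitlist against treatment; Background and Rationale presents the waitlist period as part of what makes this trial more stringent than the uncontrolled pilot. A difference between two adjacent changes is estimated much less precisely than one change, because the shared T1 measurement enters both with opposite sign. Power computed for one change, or for a correlation, therefore does not carry over.

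The stated model does not visibly contain the comparison either. Two latent variables in a growth model are normally an intercept and one slope or shape factor; separate waitlist and treatment slopes normally need a third.

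If the sentence stands, a null result for the primary contrast may be read as negative evidence from a trial with 80% power. Interpretation could then fall back on the T1 to T3 change alone, the uncontrolled estimate that the waitlist was added to improve on.

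**Working it through.** **Inputs from the article.** n = 90; effect 0.3; α = .05 (two-sided assumed, because it reproduces 90); power .80; 2 latent variables; wait W = 4 to 6 weeks; group period 6 weeks; booster at 10 weeks; QPR test-retest ICC 0.74. **Assumptions of this check.** Equal correlations and variances across visits, no change over the waitlist, no slope heterogeneity, and 90 people with usable data.

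**1. Reproducing 90.** Two routes give it.
- Paired t test, one change of 0.3 in units of its own SD, two-sided, noncentral t: power is 79.9% at n = 89 and 80.4% at n = 90.
- A-priori structural equation lower bound for a latent correlation: n = {K + H + √[(K + H)² + 4AH(π/6 + √A + 2B − C − 2D)]}/(2H). Here K = A(π/6 − B + D), A = 1 − ρ², B = ρ·arcsin(ρ/2), C = ρ·arcsin(ρ), D = A/√(3 − A) and H = (δ/(1.960 + 0.842))². With δ = ρ = 0.3, K + H = 1.020 and H = 0.01147, so n = 89.1, rounded up to 90. (With ρ = 0 the same formula gives 108.4.)

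The first route tests one change against zero and the second a correlation. Neither tests a difference between two trajectories.

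**2. Variance of the primary contrast.** Take the weekly rate from T1 to T3 minus the weekly rate from T0 to T1. Relative to the variance of the T1 to T3 rate alone, the variance ratio is

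(1/36 + 1/W² + (1/6 + 1/W)²) / (2/36).

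This gives 4.75, 3.64 and 3.00 for W = 4, 5 and 6, so the standard error is 2.18, 1.91 and 1.73 times larger.

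**3. Reading A: 0.3 is one standardised change.** The standardised contrast is 0.3 divided by the standard-error ratio.

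| Wait (weeks) | Standardised contrast | Power at n = 90 |
|---|---|---|
| 4 | 0.138 | 25% |
| 5 | 0.157 | 31% |
| 6 | 0.173 | 37% |

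At a 6-week wait, 80% power would need 264. AR(1) correlations of 0.3 to 0.8 with equal periods raise power only to 40% to 48%. If total changes rather than weekly rates are compared, the 6-week figure applies to any wait under equal correlations.

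**4. Reading B, a separate scenario: 0.3 is in outcome-SD units, with an assumed between-visit correlation of 0.74.** The contrast is 0.3/6 = 0.05 SD per week, with unit variance 0.26 × (1/36 + 1/W² + (1/6 + 1/W)²).
- T1 to T3 against T0 to T1: power is about 43%, 53% and 62% for W = 4, 5 and 6.
- One treatment slope that continues undiminished to T4 (generalised least squares on T0, T1, T3, T4): about 57%, 71% and 81% by normal approximation, and about one percentage point lower with the t distribution.

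On this scale one change is 0.3/√(2 × 0.26) = 0.416 of its own SD and has 97% power at n = 90. Reading B is therefore incompatible with 90 being the size for one change, and its figures should not be merged with those of Reading A into one range.

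**5. Reading C: 0.3 is the standardised contrast itself.** Power at 90 is 80.4%.

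**6. Detectable contrast at n = 90 with 80% power.** A standardised effect of about 0.30 is detectable. In SDs of one 6-week change this is 0.30 × 2.18, 1.91 and 1.73 = 0.65, 0.57 and 0.52 per 6 weeks. Multiplied by √0.52 = 0.721, it is 0.47, 0.41 and 0.37 outcome SD, against 0.30 × 0.721 = 0.22 outcome SD for one change.

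**The case against.** The strongest reply is that the article nowhere says 90 came from a test of one change. It says a growth curve structural equation model, and a structural equation formula gives the same 90. This stands. A reader might infer from the match with the paired t test that this is how 90 was obtained, but the match is not unique, and 0.3 is more usually called medium for a correlation. It does not rescue the 80%, because a latent correlation is not the waitlist-versus-treatment contrast either.

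A reader might also infer that the 80% is simply wrong. The article does not support that: if 0.3 is the standardised contrast, power is about 80%, and nothing excludes this reading. Nothing states it either.

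Reading B leans on a test-retest figure from the literature, which is not this trial's correlation between visits. Higher or differently patterned correlations give more power on that scale. With equal 6-week periods, power is 73% at an equal correlation of 0.8, and 74% and 85% under AR(1) at 0.74 and 0.8.

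Using T4 also helps. But the higher figures in Reading B need one undiminished slope to the booster, whereas Objectives predicts slower improvement after the group ends.

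The exact coding of the slopes may properly sit in the full protocol or analysis plan. The point here is not that missing detail. It is that a stated power is attached to the primary model without inputs that correspond to the primary contrast. The recruitment arithmetic is not at issue: 160 × 0.6 = 96, above 90.

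**Conclusion.** The concern holds as a mismatch between the stated power and the primary comparison. The inputs given (one effect of 0.3 on no stated scale, two latent variables) do not describe a difference between two trajectories, so the 80% cannot be confirmed for it.

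The size depends on what 0.3 means. As one standardised change, power is about one quarter to three eighths. In outcome SDs with an assumed correlation of 0.74, it is about 43% to 62%, or 57% to 81% with an undiminished slope to the booster. Of the three readings worked through, power reaches about 80% only where 0.3 is the contrast itself, or in that last scenario with a 6-week wait. All figures assume 90 analysable participants and no slope heterogeneity. All but Reading C also assume no waitlist change, which is what Objectives predicts; an improvement during the wait would shrink the contrast and lower the power. Confidence is medium, because the scale of 0.3 and the trial's own correlations are unknown.

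**What to change.** Restate the power sentence for the primary contrast. Name the contrast (for example, the T1 to T3 rate minus the T0 to T1 rate, or a single treatment slope to T4 minus the waitlist slope). State the scale of 0.3 and the assumed correlations between visits. Give the power, or the contrast detectable with 80% power, at n = 90 for waits of 4, 5 and 6 weeks. If 0.3 is not the standardised contrast, say plainly that the 80% does not apply to the waitlist-versus-treatment comparison.

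This takes a few sentences and changes nothing in enrolment, assessments or the model. The cost is a stated figure that will probably be less favourable. The Results section reports that no data analysis had been conducted at submission, so a restatement made before any analysis would not be informed by results.

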### Outcomes

#### Timeline

The schedule of enrollment, interventions, and assessments is displayed in Figure 2. The quantitative self-report outcome measures are intended to be completed independently at the start of the waitlist period (T0, approximately 4-6 weeks before the start of the group program, typically at the “Information and Engagement” session), at the start of the group program (T1), at the end of the group program (T3, which is 6 weeks after the start of the group program), and at the booster session (T4, about 10 weeks after the start of the group program). Some participants may complete outcome measures at the midpoint session (T2, which is 3 weeks after the start of the group program) if the study site is resourced to collect data at an additional time point. Measures are completed after the group session, except for at T1, when participants complete measures before the start of the group to ensure no exposure to the program’s content. Participants can request assistance from facilitators to complete the measures. Demographic and clinical information will be obtained from participants’ electronic health records at T0 and will include their date of birth, gender, ethnicity, country of birth, highest level of educational attainment, highest level of employment, current employment status, primary mental health file diagnosis, co-occurring mental health file diagnoses, date of first contact with mental health services, number of listed episodes of outpatient mental health care, and number of psychiatric admissions.

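### The process test leaves first-half recovery change out of its stated terms, so a significant result cannot by itself show that flexibility change comes before recovery change

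*Protocol article*

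**What the plan says.** Under Objectives, the protocol article gives a time-ordered hypothesis, with the recovery change placed in the later half of the sessions: "changes in psychological flexibility processes during the first half of the group program will be associated with changes in personal recovery and well-being". The same section expects recovery and the secondary outcomes, which include the four process variables, to follow one course after the waitlist: they "then will improve from the start to the end of the group program, and then improve at a less rapid rate" up to the booster session.

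Statistical Methods and Sample Size gives the test, to be run only if there are enough data. Its predictor is "the trajectory of the 4 psychological flexibility process variables from the start of the group to the midpoint session (T1 to T2"). The question put to the data is whether that early process change "is significantly associated with the trajectory of personal recovery (T2 to T4) using multivariate growth models". Neither window contains recovery change from T1 to T2. The sentence mentions no conditioning on that change and no test in the reverse order.

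The Timeline section makes T2 optional and dependent on site resources: "Some participants may complete outcome measures at the midpoint session (T2, which is 3 weeks after the start of the group program"). Where T2 is collected, the outcome measures are completed together, so early recovery change is observable in the participants who enter this test.

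**The concern.** Research question 3 already asks whether process change and recovery change go together. The lag is the only thing the further hypothesis adds.

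Suppose people differ in how fast they improve. A fast improver gains on flexibility and recovery together in the first half and keeps gaining on recovery in the second. Early flexibility change then stands in for early recovery change, and the stated association appears even if flexibility adds nothing to later recovery. The article's own expectation of joint improvement makes this plausible. So does one reading of its "growth curve structural equation model (5 observed variables and 2 latent variables"): with one intercept and one slope, each person has a single rate of change across both halves.

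A positive result could then be written up as evidence of ordering when the data show only concurrent improvement.

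**Working it through.** **The plan's own figure.** The process test has no sample size of its own. The stated minimum of 90 (effect 0.3, α .05, power .80) reproduces: the usual a-priori lower bound for a structural equation model with 2 latent variables gives 89.1, rounded up to 90. Allowing for 60% retention, 90/0.6 = 150, and 160 × 0.6 = 96, so the target of 160 covers it. This figure is not in dispute and is used below only as a convenient n.

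**Inputs that are assumptions.** The article gives neither correlation.
- a = correlation of process change and recovery change over T1-T2: 0.5 (range 0.3 to 0.7).
- b = correlation of early (T1-T2) and later (T2-T4) recovery change: 0.6 (range 0.4 to 0.8; zero is treated separately).
- Lagged process effect: zero. Test two-sided at 0.05.

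**Step 1, error-free scores.** By path tracing, the tested correlation is a × b = 0.5 × 0.6 = 0.30 (range 0.3 × 0.4 = 0.12 to 0.7 × 0.8 = 0.56). By Fisher's z with n=90, the rejection probability is 82% at 0.30, 20% at 0.12 and about 100% at 0.56. With n=45 and correlation 0.30 it is 52%. With true early recovery change in the model, simulated rejection returns to about 5%.

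**Step 2, scores with error.** The Primary Outcome section gives a test-retest ICC of 0.74 for the recovery measure. Treating the remainder as error, the error SD is √(1 − 0.74) = 0.51 score SDs. Error equal to 0.5 true-change SDs then implies a true-change SD of 0.51/0.5 = 1.02 score SDs over three weeks. Error equal to 1.0 implies 0.51. The first is a large amount of true change for three weeks, so the lower rows below deserve at least as much weight. Simulated rejection using observed change scores (n=90, a=0.5, b=0.6, equal error in both measures):

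| Error SD / true-change SD | Independent errors | Same-visit errors correlated 0.4 |
|---|---|---|
| 0.5 | 48% | 24% |
| 0.73 | 27% | 6.5% |
| 1.0 | 15% | 6%, mean correlation slightly negative |

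Correlated same-visit errors pull the association down because the T2 recovery score ends the first window and starts the second.

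**Step 3, no persistence.** If b = 0, rejection is about 5% with error-free scores or independent errors. With same-visit errors correlated 0.4 it is 9% (error SD 0.5) and 25% (error SD 1.0), but the mean correlation is negative (−0.06 and −0.13). That is the opposite direction to general improvement.

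**Step 4, does simple adjustment work?** Not with observed difference scores. With independent errors, b = 0.6 and error SD 0.5 to 1.0, regression on observed early recovery change still rejects in about 21-28% of runs. At error SD 1.0 that is more often than without adjustment.

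**The case against.** The strongest reply is that the test matches the hypothesis as worded. Both say associated, and neither claims an effect beyond early recovery change. In the scenario above, the population association really is 0.30, so rejecting no association is correct, and 82% is power for a true association. This stands. A reader might infer that the test has an 82% false-positive rate; the article does not support that. The figure becomes an error rate only if the result is read as time order, which is the reading the first-half to second-half wording invites.

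Second, a condensed article names the two windows and a model family, not the full specification. A reader might infer that the model excludes all recovery data before T2. The text does not say so, and the full protocol or analysis plan may add terms. What the text does fix is the pair of quantities whose association is tested, and that pair does not isolate the lag. The lack of a reverse-order test is only an omission and carries no weight alone.

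Third, error-free scores are the most favourable case for the concern, and neither correlation is documented. This also stands, which is why the size is given as a wide range.

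Fourth, if flexibility works through early recovery, conditioning on early recovery removes that route and changes the question. This is a good reason to report the conditional path beside the stated association, not in place of it.

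**Conclusion.** The point holds in a limited form. As stated, the process test cannot distinguish a first-half to second-half ordering from general improvement. A significant result can arise with no lagged process contribution, provided that early process and early recovery change are correlated and that recovery change persists into the second half.

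How often this would happen is not known. At n=90, with assumed correlations 0.5 and 0.6, it ranges from about 82% with error-free scores down to about 6% with substantial, correlated error. With no persistence of recovery change there is no association in the hypothesised direction beyond chance.

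A reader might go further and conclude that the trial's main result is compromised. The documents do not support that. This analysis is secondary, depends on sufficient data from an optional visit, and touches neither the primary outcome nor the sample size. The Discussion already limits causal conclusions because the trial is not randomised.

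**What to change.** In the conditional process analysis:
- Start the recovery curve at T1, with separate T1-T2 and T2-T4 change.
- Use a multivariate latent change or piecewise growth model with measurement error modelled, drawing on all available waves. Do not use observed difference scores: two visits alone cannot separate error from true change, and the T2 recovery score belongs to both windows.
- Report the path from process change T1-T2 to recovery change T2-T4 conditional on latent recovery change T1-T2, alongside the stated unadjusted association.
- Report the mirror path (recovery change T1-T2 to process change T2-T4) descriptively. A rule that the forward path must exceed it is not needed.
- Describe the finding as time-ordered only if the conditional path is supported. Otherwise call it an association that may reflect concurrent improvement.

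The cost is plan wording and some additional model runs, with no new data collection. The Results section says no analysis had been done at submission, so this could still be specified in advance. The downsides are a wider interval for the process path and possible non-convergence in the optional T2 subset, so the wording should say that the unadjusted association, labelled as such, will be reported if the fuller model cannot be fitted.
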